### The Integrated PMRT and Virtual Environment Design

The virtual environment design and the hardware and software equipment are described in the paper by Pardini et al [39], in which the aim was to investigate the user experience, preferences, and engagement of the exposure to personalized, natural, and realistic VR scenarios.

Specifically, we adapted the procedure that Baird and Sands [19] introduced to propose an integrated intervention using different new technologies.

The protocol concerns the learning of the adapted abbreviated PMRT [33] in 5 sessions 2 times a week, as follows:

Four sessions of active progressive muscle relaxation, in which participants are required perceptively learn the differences between the tension and relaxation of different muscle sections of the body. Each session has a duration of approximately 25 minutes. The first session is dedicated to the hands, forearms, arms, neck, shoulders, and back; the second to the facial muscles; the third to the diaphragmatic breathing; and the fourth to the abdomen, buttocks, and lower limbs. These sessions take place via the Zoom platform and are conducted by a cognitive-behavioral psychotherapist. Each Zoom session consisted of filling out 2 measures for the state anxiety and relaxation state based on the Moodle e-learning platform, sharing general standardized instructions for conducting relaxation and the rationale of the PMRT, guided relaxation aimed at relaxation of a dedicated body site, and filling out the same measures administered at the beginning of the session. A profile was created for each participant to access the Moodle platform. For the participants in condition “intervention B” (described in the following section) who participated in the first 4 PMRT sessions through the audio-track, all sessions were self-managed within the Moodle platform. Various activities have been scheduled based on the beginning of the training and the end of the activities planned in previous sessions.The fifth VR session is administered at the University of Padova Laboratory. All participants are asked to wear a smartwatch for heart rate detection. A total of 5 measurements (1 per minute) are made before the VR experience, 12 during the entire exposure in the virtual environment, and 5 after the experience in the virtual context. A duration of approximately 12 minutes has been established to avoid potential cybersickness symptoms during the virtual experience. This brief relaxation session is practiced by inexperienced individuals allowing for a decrease in anxiety and negative mood [40,41].

### Study Design

The present protocol of the proof-of-concept study is a longitudinal, between-subjects, 3-armed randomized controlled trial aiming to compare three treatment conditions (Figure 1):

Active Comparator condition, consisting of the deployment of the PMRT training via Zoom and GI exposure. It consists of a standard behavioral intervention based on 4 individual PMRT sessions via Zoom (t1-t4), an in vivo PMRT relaxing session and GI conducted by a psychotherapist (T1) after a week from the baseline assessment (T0), and a follow-up phase (T2) after 2 weeks consisting in recovering the GI relaxing scenario and PMRT session (see Multimedia Appendix 1 and Figure 2).Intervention A is an experimental condition in which the complementary intervention is composed of the PMRT administered via Zoom integrated with a personalized VR exposure deployed by a head-mounted display (Oculus Quest 2). It comprises 4 individual PMRT sessions via Zoom (t1-t4), an in vivo PMRT relaxing session and VR exposure (T1) after a week from T0, and a follow-up phase that consists of the same activities as the Active Comparator condition (see Multimedia Appendix 1 and Figure 3).Intervention B is an experimental condition in which the complementary intervention is composed of progressive muscle relaxation training administered through an audio-track integrated with the same personalized VR exposure setup in Intervention A. It is composed of 4 individual PMRT sessions via an audio-track delivered on the Moodle platform (t1-t4), an in vivo PMRT relaxing session and VR exposure (T1) after a week from T0, and a follow-up phase that consists of the same activities as the Active Comparator and the Intervention A conditions (see Multimedia Appendix 1 and Figure 4).

The assessment phases take place at baseline (T0), before and after the 4 PMRT sessions (via Zoom or audio-track), at the fifth in-presence session (T1), and a week later (T2).

The T0 (baseline) assessment phase has a duration of approximately 37 minutes, is the same for all participants, and is administered at the Virtual Reality Laboratory (A10-A11), Department of General Psychology, University of Padova (Italy). In this phase, the following measures are administered: (1) a demographic schedule (addressing age, gender, nationality, mother tongue, marital status, years of school attendance, employment status, psychological problems or disorders, ongoing psychological treatment, drug use, medical conditions, neuromuscular issues, previous injures, previous experiences in relaxation practice or anxiety management training, or with Oculus), and also, refraining from smoking, intense physical exercise, consuming caffeine for at least 1 hour before testing, and consuming alcohol for at least 6 hours before testing [42]; (2) a series of self-report questionnaires investigating depression, anxiety, stress, quality of life, and distress coping strategies (State Trait Anxiety Inventory-Y [STAI-Y], Depression Anxiety Stress Scales-21 [DASS-21], Psychological General Well-Being Index [PGWBI], and COPE-NVI); and (3) resting heart rate detection with an Mi Band 2 sensor.

Before and after each relaxation session (t1-t4), in approximately 20 minutes, the personal level of tension is assessed by using a visual analog scale from 0 (no tension) to 10 (extreme tension level). The state-anxiety level is evaluated based on the STAI-Y1. The 4 relaxation sessions are administered 2 to 3 days apart from each other for all 3 groups. The assessment phase is administered through Moodle, an e-learning platform used for data collection.

The T1 phase (day 7) required approximately 60 minutes. Before and after the relaxation session, states of tension and anxiety are assessed by using a 0 (no tension) to 10 (extreme tension level) scale, and the state-anxiety level is evaluated based on the STAI-Y1. Then, participants are exposed to a PMRT session merged with a VR or a GI procedure. Before the GI or the VR experience, all the participants fill out the Vividness of Visual Imagery Questionnaire and the Test of Visual Imagery Control. After the PMRT session, users compile a series of self-report questionnaires investigating depression, anxiety, stress, and quality of life (STAI-Y, DASS-21, PGWBI), and the VR group only fill out the Virtual Reality Sickness Questionnaire to monitor VR-related side effects (eg, sickness) and the ITC-SOPI to assess the sense of presence at the end of the T1 phase. The Mi Band 2 sensor is used during the entire T1 phase administration to detect resting heart rate activity. This assessment phase is administered through the Moodle e-learning platform.

The T2 phase (follow-up) is deployed for approximately 45 minutes. Before and after the relaxation session, states of tension and anxiety are assessed using a visual analog scale from 0 (no tension) to 10 (extreme tension level). The state-anxiety level is evaluated based on the STAI-Y1. All the users are exposed to a self-GI experience in which those who were part of the VR group are asked to recall the personalized VR scenario experienced during the T1 phase (day 7). Instead, the GI group retrieve the image participants had used in association with the PMRT during the T1 phase (day 7). After the session, participants fill out a series of self-report questionnaires investigating depression, anxiety, stress, quality of life (STAI-Y, DASS-21, PGWBI), and an ad hoc version based on the ITC-SOPI to assess the sense of presence experienced during the imagery experience. This assessment phase is administered based on the Moodle e-learning platform. The Mi Band 2 sensor is used during the entire T1 phase administration (day 7) to detect resting heart rate activity.

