### Study Overview and Objectives

The purposes of the present research project are as follows:

Investigating if PMRT associated with a personalized relaxing scenario in VR can facilitate relaxation and lower state anxietyUnderstanding if the VR scenario helps recall the relaxing image assessed during the follow-up sessionInvestigating if VR is more effective in promoting the association between the relaxing scenario and PMRT than the standard procedure, consisting of PMRT associated with the imagery-induced exposure to a subjective relaxing environmentAnalyzing if the relaxing sessions administered via Zoom are more effective in managing anxiety and stress than a procedure administered via audio-tracks.

We hypothesize that VR would be more effective than GI in promoting relaxation and decreasing state anxiety because it would facilitate the visualization process, allowing individuals to have more realistic sensory experiences than imagery-induced exposure.

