### Measures-Screening and Primary Outcomes

In Table 1, all the assessment and primary outcome measures are described.

**Table 1 table1:** Evaluation tools and methods by outcome of interest.

Primary objective	Description	Evaluation tool
1. Number of participants with virtual reality (VR)–related side effects as assessed by the Virtual Reality Sickness Questionnaire (VRSQ) and the investigators’ observations^a^	Participants in the 2 VR experimental arms (Interventions A and B) are asked to refer to whether the VR head-mounted display was painful, too heavy, or uncomfortable. Participants are asked if they have experienced negative side effects during the VR exposure based on the VRSQ, administered at the end of the VR exposure. This questionnaire is based on a dichotomous answer (Yes/No). During the VR experience, the investigator observes participant reactions and records the behaviors and signs that suggest an unpleasant experience.	VRSQ [44,45]
2. Changes between and within subjects in depression scores^b^	Differences between groups and change from baseline to the T1 and T2 phases in depression scores are assessed based on the Depressive Anxiety Stress Scale-21 (DASS-21-Depression Subscale). Items are answered using a 4-point Likert scale (0-3). Scores range from 0 to 42 (the scores will need to be multiplied by 2 to calculate the final score). Higher scores indicate more severe depression.	DASS-21-Depression Subscale [46-48]
3. Change is being assessed between and within subjects in trait-anxiety scores^b^	Differences between groups and change from baseline to the T1 and T2 phases in trait-anxiety scores are assessed based on the State-Trait Anxiety Inventory-Y2 (STAI-Y2, Trait Anxiety). The measure is a self-report questionnaire investigating trait anxiety based on a 4-point Likert scale (1-4). Scores range from 20 to 80. Higher scores indicate higher trait-anxiety severity.	STAI-Y2 [49-51]
4. Changes between and within subjects in state-anxiety scores^b^	Differences between groups and change from baseline to the T1 and T2 phases in state-anxiety scores are assessed based on the State-Trait Anxiety Inventory-Y1 (STAI-Y1, State Anxiety) before and after each session. The STAI-Y1 is a self-report questionnaire investigating the state anxiety based on a 4-point Likert scale (1-4). Scores range from 20 to 80. Higher scores indicate greater state-anxiety severity.	STAI-Y1 [49-51]

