### Statistical Procedure and Data Analysis

Quantitative statistical analyses will be performed using SPSS (versions 27.0 and 28.0; IBM Corp) [60,61] and R package [62]. To investigate the normal data distributions of the dependent variables, ranges of skewness and kurtosis will be determined. The Kolmogorov-Smirnov and the Shapiro-Wilk tests will also be performed to evaluate the statistical significance (mean, 95% CI) and normality of the distributions. In addition, Cronbach α will be assessed for each self-report questionnaire’s subscales. To explore sociodemographic features, frequencies, means, and SDs will be measured.

To examine differences between and within subjects, the 3 groups will be evaluated by a repeated-measures ANOVA for mixed designs, where individuals will be the random effect, while the type of intervention and time (T0/T1/T2/before and after each session) will be the fixed effects. The Akaike information criterion and binary logistic regression will be performed to explore significant influence factors.

Spearman rank correlation coefficient will be used to investigate the relationship between the self-reported measures and heart rate.

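### The VR versus GI hypothesis is not tied to T1, the only visit at which the arms differ in exposure, and the trial is sized on a group effect averaged over T0, T1 and T2

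*Protocol article*

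**What the plan says.** **Exposure.** Under Study Design, at T1 "participants are exposed to a PMRT session merged with a VR or a GI procedure". At T2, "All the users are exposed to a self-GI experience in which those who were part of the VR group are asked to recall" the personalised scenario from T1, while the GI group retrieves its own T1 image. The headset is not used at T2.

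**Aims.** Study Overview and Objectives gives recall of the relaxing image at follow-up as an aim of its own. The hypothesis is stated separately and without a visit: "We hypothesize that VR would be more effective than GI in promoting relaxation and decreasing state anxiety".

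**Outcome.** Table 1, outcome 4: "Differences between groups and change from baseline to the T1 and T2 phases in state-anxiety scores are assessed" with the STAI-Y1. Neither visit is singled out.

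**Analysis.** Statistical Procedure and Data Analysis plans a mixed-design repeated-measures ANOVA in which "the type of intervention and time (T0/T1/T2/before and after each session) will be the fixed effects". It names no group-by-time term and no visit-specific contrast.

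**Sample size.** Power Calculation uses the between-factors repeated-measures ANOVA with effect size 0.25, alpha .05, power 0.80, 3 groups and 3 measurements. This gives at least 36 per group.

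**T2 wording.** The Active Comparator's follow-up is described as "recovering the GI relaxing scenario and PMRT session". Intervention A has "a follow-up phase that consists of the same activities as the Active Comparator condition".

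**The concern.** T1 and T2 answer different questions. At T1 the arms differ in what participants experience during the session. At T2 everyone performs the same kind of self-guided exercise, and what differs is what they received at T1. The reason given for expecting VR to win, a more realistic sensory experience, applies while VR is in use. A lasting benefit at T2 is possible, but it is a different claim.

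A group main effect from the planned ANOVA combines these two visits with a baseline taken before any intervention. If the T1 advantage is not fully carried to T2, this average understates it, and a real T1 benefit may be missed. Because no visit is named for the hypothesis, the T1 result, the T2 result and the average could each later be offered as its test.

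**Working it through.** **Inputs from the Power Calculation.** k = 3 groups, m = 3 occasions, f = 0.25, alpha = 0.05, N = 108.

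**Assumptions not in the document.** Correlation rho between occasions (0.5, range 0.3 to 0.7), equal SDs, the same correlation between all pairs of occasions, and the size of the T2 effect relative to T1.

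**Step 1. Reproduce the plan's figure.** For the between-factors test the noncentrality is lambda = N f² m / [1 + (m − 1) rho], with k − 1 and N − k degrees of freedom. At rho = 0.5:

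lambda = 108 × 0.0625 × 3 / 2 = 10.125 on 2 and 105 df, power 0.81.

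This is the smallest equal allocation reaching 0.80, so 36 per group is reproduced. The group-by-time version with the same inputs needs only 36 participants in total and does not give 108. The sized test is therefore the group effect averaged over occasions.

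**Step 2. Let the effect vary by occasion.** Keep f = 0.25 at T1 and let the T0 and T2 effects be multiples of it. The averaged effect is 0.25 × (T0 + T1 + T2 multiples) / 3, put into the same formula with N = 108.

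| Multiples at T0, T1, T2 | Mean f | lambda (rho 0.5) | Power, rho 0.5 | Power, rho 0.3 to 0.7 |
|---|---|---|---|---|
| 1, 1, 1 (implied by the plan) | 0.250 | 10.125 | 0.81 | 0.89 to 0.73 |
| 0, 1, 1 | 0.167 | 4.50 | 0.45 | 0.54 to 0.38 |
| 0, 1, 0.5 | 0.125 | 2.53 | 0.27 | 0.33 to 0.23 |
| 0, 1, 0 | 0.083 | 1.125 | 0.14 | 0.17 to 0.13 |

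The first row needs a group difference at T0, which randomisation rules out in expectation. Setting T0 to zero takes power from 0.81 to 0.45 even with full carry-over to T2. That loss does not depend on what happens at T2. Any further loss depends on how much of the effect survives.

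**Step 3. Group-by-time test.** For the pattern 0, 1, c at rho = 0.5 and N = 108, its power is 0.65 (c = 1), 0.51 (c = 0.5) and 0.65 (c = 0). It can detect a difference confined to T1, but at this effect size it does not reach 0.80 either, and it does not say at which visit the arms differ.

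**Step 4. Power at T1 alone, three arms, f = 0.25.**

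- Unadjusted: lambda = 108 × 0.0625 = 6.75, power 0.63; N = 159 needed for 0.80.
- Adjusted for T0: lambda = 6.75 / (1 − rho²). At rho = 0.5 this is 6.75 / 0.75 = 9.0 on 2 and 104 df, power 0.76, N = 120 needed. At rho = 0.3 and 0.7, power is 0.67 and 0.90 (N = 144 and 84).

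**Step 5. The two-arm contrast.** Intervention A versus Active Comparator has 36 v 36. Taking 0.5 SD as an assumed difference, power is 0.55 unadjusted. Adjusting for T0 at rho = 0.5 gives 0.5 / √0.75 = 0.577 residual SD and power of about 0.68 (t test, 69 df).

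**The case against.** **T2 is deliberate.** It is labelled follow-up, has its own objective, and fits the conditioning rationale in the Introduction. This stands. Withdrawing VR at T2 is not a design error, and a T2 difference between Intervention A and the comparator is a legitimate carry-over effect of the randomised T1 exposure.

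**The ANOVA can keep the visits apart.** Time is a factor, a mixed-design ANOVA can show a group-by-time difference, and the preliminary Results report VR versus GI at T1 separately. This also stands in part. A reader might infer that the protocol declares T1 and T2 to be two readings of one effect; it does not say so. But being able to separate visits is not the same as naming which one tests the hypothesis, and the only test given a sample size is the averaged one.

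**The exact contrast may sit in a fuller plan.** It may. The point rests on what the article itself fixes: a sample size built on the between-factors effect over three measurements.

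**The true effect may be large.** The preliminary T1 means (30.10, SD 4.35 v 39.35, SD 4.71) differ by 9.25, about 2.0 pooled SDs. An effect of that size would survive considerable dilution. The figures are early, from about 40 participants, and the sample size rests on f = 0.25, so the calculation above stays with the plan's own assumption.

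**Stronger readings that fail.** A reader might infer that including T2 could reverse the result. The mean of T1 and T2 changes sign only if the T2 effect is opposite and larger, and no T2 result is reported. A reader might also infer that the arm effect answers neither aim. That goes too far, since T2 does address recall.

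**The T2 descriptions.** A reader might see a contradiction in giving the VR arms the comparator's follow-up when they had no GI scenario. The later T2 paragraph states what each group recalls, so this is loose wording only.

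**Conclusion.** The concern holds in this form: the VR versus GI hypothesis is not tied to the one visit where exposure differs, and the test that was sized averages over a baseline with no expected effect and a follow-up without VR. At f = 0.25, N = 108 and rho = 0.5, the stated power of 0.80 becomes 0.45 with full carry-over to T2 and 0.14 with none (0.54 to 0.38 and 0.17 to 0.13 for rho 0.3 to 0.7). The T0 part follows from randomisation. The T2 part is conditional on carry-over, about which the document gives no data. The correlation, equal SDs and equal correlations are assumptions. The change is worth making because it is cheap and removes an ambiguity over the main claim; it does not imply that the design or the T2 visit is wrong.

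**What to change.** 1. In Study Overview and Objectives and in Statistical Procedure and Data Analysis, name T1 post-session state anxiety (STAI-Y1), Intervention A versus Active Comparator, adjusted for T0 state anxiety, as the test of the VR versus GI hypothesis.
2. Name the same contrast at T2 as a separate test of recall or carry-over after VR has been withdrawn.
3. State that the occasion-averaged arm effect will be used for neither.
4. Restate the power for T1. For three arms at f = 0.25 and N = 108 it is 0.63 unadjusted and about 0.76 adjusted for T0 at rho = 0.5. Give the assumed correlation, and also the power of the two-arm contrast, which is lower under the assumption in Step 5.
5. Align the follow-up wording in the arm descriptions with the T2 paragraph of Study Design.

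Cost: protocol and analysis wording plus a revised power statement. No new assessment is needed, since state anxiety is already scheduled at T0, T1 and T2. The article describes the study as ongoing, with preliminary T1 comparisons already made, so the change should be dated and that fact disclosed. The downside is that the stated power becomes less favourable.

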**Figure 1 figure1:**
[figure not shown]
Consolidated Standards Of Reporting Trials 2010 flowchart. GI: guided imagery; PMRT: progressive muscle relaxation technique; VR: virtual reality.

**Figure 2 figure2:**
[figure not shown]
Graphic description of the activities carried out during the Active Comparator condition: progressive muscle relaxation technique (PMRT) training via Zoom and guided imagery (GI) exposure.

**Figure 3 figure3:**
[figure not shown]
Graphic description of the activities carried out during the Intervention A: PMRT training administered via Zoom integrated with a personalized virtual reality exposure deployed by a head-mounted display (Oculus Quest 2). GI: guided imagery; PMRT: progressive muscle relaxation technique.

**Figure 4 figure4:**
[figure not shown]
Graphic description of the activities carried out during the Intervention B: PMRT training administered based on the Moodle platform via an audio-track integrated with a personalized virtual reality exposure deployed by a head-mounted display (Oculus Quest 2). GI: guided imagery; PMRT: progressive muscle relaxation technique.

### Power Calculation

Sample size estimation was computed with G*Power 3.1 software (Heinrich Heine Universität Düsseldorf) [43]. As a statistical test, the repeated-measures ANOVAs between factors have been considered. The effect size was set as 0.25, the α as .05, and the Power (1β error probability) as 0.80. We have 3 separate groups and 3 measurements. On the basis of these parameters, we estimated having to recruit at least 36 participants for each of the 3 groups.

### Data Collection, Storage, and Security

Based on informed consent, participants are informed about the experimental procedure; how data are collected, transmitted, and stored; and who has access to the data. Any digital data, such as responses to web-based questionnaires, are uploaded and saved to a secure server. Any hard copy documents are stored in a locked cabinet. Both digital data and hard copy documents are retained for 10 years after the end of the study and then securely destroyed.

